## Abstract

**Background:**

Previous studies have demonstrated that adverse events occur during chiropractic treatment. However, because of these studies design we do not know the frequency and extent of these events when compared to sham treatment. The principal aims of this study are to establish the frequency and severity of adverse effects from short term usual chiropractic treatment of the spine when compared to a sham treatment group. The secondary aim of this study is to establish the efficacy of usual short term chiropractic care for spinal pain when compared to a sham intervention.

**Methods:**

One hundred and eighty participants will be randomly allocated to either usual chiropractic care or a sham intervention group. To be considered for inclusion the participants must have experienced non-specific spinal pain for at least one week. The study will be conducted at the clinics of registered chiropractors in Western Australia. Participants in each group will receive two treatments at intervals no less than one week. For the usual chiropractic care group, the selection of therapeutic techniques will be left to the chiropractors' discretion. For the sham intervention group, de-tuned ultrasound and de-tuned activator treatment will be applied by the chiropractors to the regions where spinal pain is experienced. Adverse events will be assessed two days after each appointment using a questionnaire developed for this study. The efficacy of short term chiropractic care for spinal pain will be examined at two week follow-up by assessing pain, physical function, minimum acceptable outcome, and satisfaction with care, with the use of the following outcome measures: Numerical Rating Scale, Functional Rating Index, Neck Disability Index, Minimum Acceptable Outcome Questionnaire, Oswestry Disability Index, and a global measure of treatment satisfaction. The statistician, outcome assessor, and participants will be blinded to treatment allocation.

**Trial registration:**

Australia and New Zealand Clinical Trials Register (ANZCTR): ACTRN12611000542998

## Background

The success of any therapy is often based on the questions "Is it safe? Is it effective?". For chiropractic therapy there has been some research to ascertain effectiveness [1] and also for spinal manipulation [2] but there has been very little to document its safety. The safety profile of any therapy is a cornerstone of modern practice as it provides protection for the public and informs the consumer consent process. Trials of chiropractic therapy have shown mixed results which, together with its current use for multiple indications, make research into aspects of its safety important.

There are several published reports about the safety of chiropractic treatment. A single arm study conducted by Senstad et al in 1996 [3] reviewed the type, frequency, and characteristics of unpleasant side effects after spinal manipulation. About half of the patients reported at least one adverse event some time during the course of a maximum of six treatments. Of these, the most common adverse events were local discomfort (53%), headache (12%), tiredness (11%), or radiating discomfort (10%). Adverse events were mild or moderate in 85% of patients. Limitations of this study included that the chiropractors gathered their own data; responders could not be compared with non-responders; and reports could not be obtained from patients who attended one treatment only. It is possible that some opted out because of unpleasant reactions, potentially making the results an underestimate.

Hurwitz et al compared the rate of adverse events between two randomly allocated groups of neck patients who received either manipulation or mobilisation from chiropractors [4]. About a third of all participants reported at least one adverse event. The most common adverse events were increased pain (27%), headache (15%), tiredness (12%), radiating pain (6%), and dizziness (4%). Participants who received manipulation were more likely to experience an adverse event than participants who received mobilisation.

A prospective survey of chiropractors in the United Kingdom examined adverse events following manipulation of the neck [5]. No serious adverse events were reported. Of the adverse events reported, the most notable were increased neck pain (7%) and increased shoulder/arm pain (4%), muscle stiffness and headache (4%). A potential limitation of this study was that data were collected by the chiropractors administering the intervention, which may have led to an underestimation of adverse events.

The fourth study was a prospective study of patients who received chiropractic care for neck pain [6]. Just over half of the participants experienced at least one adverse event following any of the three treatments, and 13% of the adverse events were severe in intensity. About 75% of all reported adverse events were musculoskeletal or pain related. Other less common adverse events included tiredness, dizziness, nausea, or ringing in the ears.

The main limitation associated with these four studies above [3-6] was that three of the studies were uncontrolled. These uncontrolled studies may have overestimated the frequency of adverse events because the reported events may be associated with either natural history [6] or a placebo response [7].

Another limitation concerns the involvement of chiropractors in collecting information about adverse events directly from the participants in two of the studies [3,5]. The involvement of chiropractors may have led to an underestimation of adverse events as the patients may have been reluctant to disclose the events they experienced.

Given the limitations associated with previous studies of adverse events during chiropractic care [3-6], it is evident that controlled studies are warranted to develop a better understanding of the rate of adverse events in chiropractic care. This proposition reflects the findings of a recent systematic review [8] that concluded there were no robust data concerning rate of adverse events after chiropractic treatment and recommended urgent investigations to provide definitive conclusions as to its safety profile.

In summary, the literature reveals that adverse events do happen from chiropractic therapies. However, previous studies have limitations and therefore we do not know the frequency and extent of these events particularly when compared to sham treatment.

## Aims

1. To establish the frequency and severity of adverse events from usual short term chiropractic treatment of the spine when compared to a sham treatment.

2. To establish the efficacy of usual short term chiropractic care for spinal pain when compared to a sham intervention.

## Materials and methods

This study will be a randomised, placebo-controlled trial comparing usual short term chiropractic care and a sham intervention of no known benefit for participants with non-specific spinal pain of more than one week in duration. The inclusion of a placebo group will allow for a comparison of adverse events between active chiropractic care and those that are a manifestation of either "sham" treatment or natural history. Participants will be randomly allocated to receive usual chiropractic care or a sham intervention consisting of non-functional therapeutic ultrasound and a de-tuned Activator^® ^instrument [9]. The reporting of the results of this trial will accord with both the extended CONSORT statement for Randomized Trials of Nonpharmacologic Treatment [10] and the CONSORT extension for Better Reporting of Harms in Randomized Trials [11].

### Study Sample and Participant Enrolment

Participants will be recruited in Perth, Western Australia by the use of newspaper advertisements. Any person who responds to the advertisement by phone will be considered a potential candidate and will receive through the mail the following documents:

• an information letter;

• a pain diagram to assess symptom location and distribution;

• the Numerical Rating Scale (NRS) [12] on which the patients will score their current overall level of spinal pain;

• Functional Rating Index (FRI) [13];

• a questionnaire enquiring about the minimum amount of change in pain levels that potential participants would consider to be an acceptable outcome [14];

• a medical history checklist.

These documents will be returned in a reply paid envelope and the information will be used to determine eligibility. To be considered for inclusion, potential participants must be adults (18 years or older), literate in English, and have had spinal pain (neck pain, mid-back pain, or low back pain) for more than 1 week. In addition, potential participants must score at least 3 on the NRS and 12 on the FRI as this allows measurement of a minimal clinically important difference in the improvement direction [15].

Potential participants will be excluded if they:

• have been previously unable to tolerate common chiropractic treatments, for example: manipulation; mobilisation; Activator^®^; flexion distraction therapy; traction; soft tissue massage; trigger point therapy; sacro-occipital technique; ultrasound; interferential therapy; and Transcutaneous Electrical Nerve Stimulation (TENS).

• have any of the following conditions: spinal pain related to cancer or infection; clinically important fracture of the spine; spondyloarthropathy; known osteoporosis; progressive upper or lower limb weakness; symptoms of cauda equina syndrome or other important neurological condition; recent disc herniation; cardiovascular disease likely to be a contraindication to spinal manipulation; uncontrolled hypertension; cognitive impairment; blood coagulation disorder; spinal surgery in the last year; previous history of stroke or transient ischaemic attacks; have a pacemaker or other electrical device implanted; are currently pregnant;

• have a current compensation claim;

• have a substance abuse problem;

• cannot commit to study protocol.

Potential participants who satisfy the inclusion criteria will be sent a more detailed information letter. Two days later, they will be contacted by phone to determine if they are interested in participating, and if so an appointment will be made to attend Murdoch University.

### Chiropractor Participants

The study interventions will be administered at the clinics of registered chiropractors in Perth, Western Australia. Recruitment of about 12 chiropractors will be by way of open advertisement to the profession using contact details in the public domain or from the online Register of Chiropractors. To be eligible, chiropractors must have had at least two years of clinical experience and regularly use spinal manipulation in the mix of their therapy modalities. Chiropractors who administer the sham intervention must have both ultrasound and Activator^® ^instruments available.

### Treatment allocation

When participants visit Murdoch University and after baseline measures and consent have been obtained, one of the research staff, excluding the research assistant (RA) and statistician, will randomly allocate the participants to one of the two groups using a 1:1 allocation. A statistician will generate a permuted block randomization sequence allocating persons to either chiropractic care or the sham group. The group assignment will be written on small cards and placed in opaque envelopes.

For ethical reasons, participants in the sham group will be offered two treatments of usual chiropractic care two weeks after receiving the last sham treatment and following receipt of their final outcome measures by the RA. Any participant who discontinues treatment will be followed-up to determine the reason for discontinuation.

### Pilot Study

A pilot study, using the first five participants recruited, will be undertaken to evaluate process and resource issues. In particular, we will examine whether the participants were able to complete the questionnaires in full without difficulty and the length of time required. All research team members involved with baseline assessments and randomisation will meet after the first five participants have been randomised to reach a consensus decision on the feasibility of administering the questionnaires. In the absence of explicit recommendations about the required sample size to examine feasibility issues, we determined that five participants would be sufficient [16].

### Intervention/treatment

Chiropractors will be asked to deliver one of the two study interventions. The study interventions are as follows:

1. Short term usual chiropractic care: a series of two chiropractic treatments to the spine as deemed suitable by a registered chiropractor. Treatments include one or more of the following: spinal manipulation, mobilisation, drop piece, traction, electro- therapies, ultrasound, Activator^®^, soft tissue techniques and other manual techniques offered by the chiropractor. This treatment approach replicates a common pragmatic approach in the field [1].

2. Sham Group: participants will receive two sessions of de-tuned ultrasound and de-tuned Activator^® ^treatment by a chiropractor to the regions where spinal pain is experienced. There is no known treatment benefit from the de-tuned ultrasound machine and it has been established in previous trials as a credible treatment option by patients [17,18]. Chiropractors will be directed to wind the Activator^® ^head force to minimum and then administer the force through a wooden tongue depressor at random locations in the spine near the areas of concern. The dimensions of the depressor are 19 mm wide and 150 mm long, although on average only 600 mm of the length will be in contact with the skin. This means a surface area of 1140 mm^2^. We measured the force this will provide to the skin using a force transducer. The mean of 5 measured attempts was a very low 3.7 kPa. To increase the perceived "hands on" credibility, the chiropractor will be trained to gently place one hand on an area adjacent to the participant's spine while delivering the ultrasound and Activator^® ^therapies. The four chiropractors recruited to deliver the sham treatment will be asked to administer the sham interventions as they normally use Activator^® ^tools and ultrasound and with the same enthusiasm they would use for all other therapies.

### Withdrawing Participants from this Study

A stopping rule was defined for withdrawing participants from this study in accordance with recommendations in the CONSORT extension for Better Reporting of Harms [11]. If a participant reports to their chiropractor or research staff a severe adverse event they will be withdrawn from the study and referred to their local doctor or hospital emergency department depending on the nature of the event. Each participant will complete an adverse event questionnaire two days after each chiropractic appointment and asked to then return it in a reply paid envelope. Any adverse event will be classified as severe if it is thought to be an emergency situation e.g. stroke or the associated pain intensity is rated above 8/10 on an 11 point NRS, which accords with the definition for a serious adverse event by Rubinstein et al [6].

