#### 3. Assessment of Adverse Event Events

To accord with the CONSORT extension for Better Reporting of Harms [11], it is necessary to *a priori *define anticipated and unanticipated adverse events and explicitly state these definitions in reporting the methods for this study. Anticipated adverse events for this study are defined as the adverse events listed in the questionnaire developed for this study and any of the other adverse events reported in the studies conducted by Senstad et al. [3], Hurwitz et al. [4], Rubinstein et al. [6], and Theil et al. [5]. Unanticipated adverse events will be defined as stroke, fracture, dislocation, or disc injury.

Information about adverse events will be collected after each chiropractic appointment. Participants will be asked to complete the questionnaire two days after each appointment as adverse events typically manifest within two days of chiropractic treatment [3,4,6].

The adverse events questionnaire [Additional file 1] was derived from a checklist used by Cagnie et al. [29]; open-ended questions from Senstad et al. [3] and Hurwitz et al. [4]; adverse events reported in RCT's [4,6,29-32]; and two surveys [5,33]. It consists of items which enquire about the onset and severity of adverse events, and items about the impact of adverse events on activities of daily living. We decided to use a questionnaire which consisted largely of predefined response options as previous studies have demonstrated that the use of predefined response options results in more comprehensive reporting of adverse events [34].

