#### 4. Assessment at Two Week Follow-Up

We will administer at two week follow-up the NRS [12], FRI [13], and the area specific instruments modified ODI [23] or NDI [24]. These questionnaires will be used to establish the short term efficacy of brief chiropractic care for spinal pain. The FABQ [19] and PCS [22] will also be administered to examine whether cognitive aspects related to the experience of pain influence pain severity, physical function and adverse events.

Also, a global measure of treatment satisfaction [27] and global measure of perceived change [35] will be administered at two week follow-up. The global measure of treatment satisfaction [27] will be used to examine the association between adverse events and treatment satisfaction. It will be measured on a five point categorical scale (very dissatisfied = 0; dissatisfied = 1; no preference = 2; satisfied = 3; very satisfied = 4). The global measure of perceived change [35] will be used to examine the association between adverse events and overall perceived change in the main complaint. It will be measured on an 11 point continuous scale varying from -5 to +5 (-5 = much worse, 0 = unchanged, +5 much better).

Blinding will be assessed at two weeks with a questionnaire [36] that asks the participants if they were in the real treatment group or the sham treatment group. The possible responses are: real treatment group; sham group; or don't know.

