#### Analysis of Adverse Events

The primary outcome (adverse event; yes/no) will be compared between groups. The severity and frequency of adverse events will be reported descriptively. Logistic regression will be used to examine associations between adverse events and several factors. Factors which have been significantly associated with adverse events in previous studies will be selected for this study. These factors comprise treatment satisfaction [4], manipulation/mobilisation [4], global improvement [4], GP visit in last six months [6], duration of neck/back pain [6], medication use [29], gender [29], and age [29]. The relative risk [39] will be calculated using a two by two contingency table and 95% confidence intervals. The number needed to harm [40] will be calculated with 95% confidence intervals to identify the number of individuals needed to be exposed to a risk factor (chiropractic treatment) over a specific period to cause harm (adverse outcome) in one patient that would not otherwise have been harmed. Data will be assessed by using per protocol analysis. In addition, an intention to treat analysis will be undertaken by using sequential regression multiple imputation [41].

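### The severe-event rule takes a participant out of the study, not only out of treatment, and leaves no stated collection of the event's later course or the two-week outcomes

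*Protocol article*

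**What the plan says.** Under Withdrawing Participants from this Study, the Protocol article says of anyone reporting a severe adverse event to the chiropractor or research staff that "they will be withdrawn from the study and referred to their local doctor or hospital emergency department". An event is severe if it is thought to be an emergency or if "the associated pain intensity is rated above 8/10 on an 11 point NRS".

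Treatment allocation uses different words for stopping treatment and gives one purpose for the contact that follows: "Any participant who discontinues treatment will be followed-up to determine the reason for discontinuation".

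The first aim is "To establish the frequency and severity of adverse events from usual short term chiropractic treatment of the spine", compared with sham. Adverse events are collected by a questionnaire due on the second day after each visit. Of that form, section 3 (Assessment of Adverse Event Events) says "It consists of items which enquire about the onset and severity of adverse events", and it adds items on daily living.

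Section 4 (Assessment at Two Week Follow-Up) collects the NRS, FRI and either the modified ODI or the NDI, and states "These questionnaires will be used to establish the short term efficacy of brief chiropractic care for spinal pain". Treatment satisfaction and perceived change are collected at the same time so that they can be related to adverse events.

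On analysis sets, Analysis of Adverse Events says "Data will be assessed by using per protocol analysis" and adds an intention-to-treat analysis by multiple imputation.

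**The concern.** Leaving treatment and leaving the study are different things, and the severe-event rule states the second. The one follow-up named elsewhere asks for the reason for stopping. In a severe-event withdrawal that reason is already known, so the contact adds nothing on how the event ran or how the participant fared.

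Three things are at stake:

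- **Course of the worst harms.** A trial whose first aim concerns harms would have no planned record of how its severe events developed after they were reported.
- **Planned associations.** Treatment satisfaction and global improvement are factors in the logistic regression for adverse events. Withdrawn participants would have neither value, so the severe cases would be missing from an analysis about adverse events.
- **Efficacy comparison.** The two-week pain and function data would be lost because of a harm. Under the plan's own rates, more would be lost from usual care.

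The Background faults an earlier study because patients may have left after unpleasant reactions. The withdrawal rule builds in a similar loss for the later data.

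**Working it through.** **Step 1: the plan's own figure.** Inputs from Sample Size: 45% versus 25%, two-sided alpha 0.05, 80% power. With pooled variance and no continuity correction:

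n = [1.960 × √(2 × 0.35 × 0.65) + 0.842 × √(0.45 × 0.55 + 0.25 × 0.75)]² / 0.20² = (1.322 + 0.555)² / 0.04 ≈ 88.1, so 89 per group.

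Power at 90 per group is 80.8%. The stated 90 per group reproduces, and this point does not dispute it.

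**Step 2: what survives withdrawal, read as written.**

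- Occurrence of the event: kept, because the report is what triggers the rule.
- Severity: kept, because the report has been classified. Onset and daily-living impact are kept if the form is returned.
- Later course, diagnosis after referral and resolution: no stated collection.
- Second adverse-event questionnaire, if the event follows the first visit: no stated collection. The form is tied to an appointment that would not take place within the study.
- Two-week NRS, FRI, ODI/NDI, satisfaction and perceived change: no stated collection.

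**Step 3: how many participants.** Let s be the share of participants with an event who have a severe one, assumed equal in both arms. Withdrawals are 90 × 0.45 × s = 40.5s in usual care and 90 × 0.25 × s = 22.5s in sham. The Background reports that 13% of adverse events were severe in an earlier neck-pain cohort. That is a share of events, not of participants, so it serves only as a middle value between 5% and 20%.

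**Step 4: effect on mean two-week pain.** Suppose those withdrawn would have scored d points above the rest of their arm. An observed-case mean is then too low by (proportion withdrawn) × d. The difference between arms is (0.45 − 0.25) × s × d = 0.20 × s × d, in favour of usual care. The documents give no value for d, so 3 to 5 NRS points is an assumption.

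| s | Usual care, of 90 | Sham, of 90 | Total | Net bias, NRS points |
|---|---|---|---|---|
| 5% | 2.0 | 1.1 | 3.2 | 0.03 to 0.05 |
| 13% | 5.3 | 2.9 | 8.2 | 0.08 to 0.13 |
| 20% | 8.1 | 4.5 | 12.6 | 0.12 to 0.20 |

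**Step 5: can the analysis repair it?** If the rule is followed, no participant with a severe event has an observed two-week score. Imputed values would rest wholly on participants without severe events, and the trial's data could not test that extrapolation.

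**The case against.** The strongest reply is that the article does not forbid further contact. A withdrawn participant also stops treatment and so falls under the follow-up sentence in Treatment allocation. Procedures after withdrawal are often left to a full protocol, which is not at hand. Figure 1 and the questionnaire (Additional file 1) are not shown either, so it is unknown whether the form asks about duration.

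Much of this stands, and it rules out three stronger readings that a reader might infer:

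- **That the outcomes are never recorded and nobody contacts the participant again.** The text says neither. It withdraws the participant and names no later collection beyond the reason for stopping.
- **That the primary outcome is lost, or that severity rests on one day-two score.** A severe event that triggers withdrawal has already been reported and classified, and the form also covers onset and daily-living impact. The per-protocol set might be thought to remove these participants from the primary comparison. If it did, the assumed rates would fall to between 43.7% versus 24.1% and 39.6% versus 21.1%, and power to between 79.5% and 74.6%, for severe shares of 5% to 20%. The document does not say that it does.
- **That the efficacy result is materially flattered.** At most 0.20 points on an 11-point scale follows, from an illustrative severe share and an unsourced pain difference. Some ratings above 8/10 may also turn out to be persisting complaints when compared with the baseline symptom checklist.

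The reply does not remove the point itself. The article states a rule, withdrawal from the study, and uses separate wording for stopping treatment. Nothing shown restores the later data. That is a rule fixed badly, not a detail merely left out.

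**Conclusion.** The point holds in a limited form. As written, the severe-event rule leaves no stated collection for the event's later course, any remaining adverse-event questionnaire or the two-week measures. The yes/no primary outcome and the reported severity need not be affected.

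About 2 to 8 usual-care and 1 to 4.5 sham participants out of 90 each would be concerned. This assumes the plan's event rates and a severe share of 5% to 20% that is equal in both arms. The bias in mean two-week pain is small under any of the values tried.

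The case for change rests on the kind of loss more than its size. It is driven by the harm under study, is probably larger in usual care, falls on the most informative safety cases, and cannot be recovered once the two-week point has passed.

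**What to change.** Leave the decision to stop treatment and refer as the investigators set it, and separate it from data collection:

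- In Withdrawing Participants from this Study, add a sentence that participants who consent remain in data collection after a severe event. This covers any remaining adverse-event questionnaire (with a due date set for it, since it is otherwise tied to an appointment), the event's outcome including the diagnosis after referral, and the two-week outcome set.
- In Treatment allocation, extend the follow-up after stopping treatment from the reason alone to the same data.

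If a fuller protocol already provides for this, the wording here only needs to be brought into line with it.

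The cost is one sentence in each section and a few extra contacts, for about 3 to 13 participants in total under the assumptions above, mostly on existing forms. The downside is a slight burden on people who have just had a severe event, and some may decline. The change has to be made before the data fall due.
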